#### 2.10.2. Maximal Strength of the Back and Hamstring Muscles

Before the test begins, the participants will be warmed up by performing two submaximal isometric contractions so as to become accustomed to the procedure. Afterwards, they will be placed into the proper position with knee and hip angles of 141° and 124°, respectively, set up by a handheld goniometer. This position corresponds to the portion of the clean lift during which the highest values of power are achieved [32]. A handlebar of this device will be attached to a floor-mounted load cell. Its height above the floor will be determined for each participant during a familiarization trial. Once the participants are in position, they will initiate the contraction after a countdown of “3, 2, 1, pull”. They will perform three maximal MVCs as forcefully as possible for at least 5 s. Participants will be provided with verbal encouragement at each trial. A minimum of a 2 min rest period will be given between MVC efforts. The visual feedback on the instantaneous force will be provided in real time on a monitor positioned in front of the research team member. Force will be measured using the FiTRO Back Dynamometer (FiTRONiC, SVK). Analog signals will be AD converted and sampled at a rate of 1000 Hz. Peak force will be analyzed.

The same system will be used for measurement of the hamstring strength. Participants, after a warm-up, will perform three 5 s isometric contractions with maximal effort on each leg at 90° of knee flexion while lying on the rehabilitation bed in the prone position. This knee flexion angle is based on findings that showed high reliability of isometric posterior lower limb muscle force [33]. In a randomized design, the left and right leg peak force will be registered. The best result from the three attempts will be taken for the analysis.

The control group without back pain will undergo the same procedures, however, these participants will also perform three MVCs as quickly and as forcefully as possible for at least 3 s. In this case, the peak RFD in addition to peak force during MVCs of the back and hamstring muscles will be analyzed.

Assessment of postural control after sudden external perturbations and maximal isometric strength of the back and hamstring muscles in participants will be completed by the measurement of their low back and hamstring flexibility.

### 2.11. Patient and Public Involvement

The public and patients will be not directly involved in the present study. Local medical centers will provide support for recruitment of physiotherapists with non-specific back pain. Test results will be provided to participants on request and the overall outcomes will be available to them on completion of the study.

### 2.12. Ethics and Dissemination

The procedures described are in accordance with the ethical standards as laid down by the 1964 Helsinki Declaration and its later amendments. Participants will be verbally informed of the main study objective, procedures, risks and benefits, confidentiality, and the voluntary nature of their participation and provided an opportunity to ask questions. Prior to inclusion, written informed consent will be obtained. Projects were approved by the ethics committee of the Faculty of Physical Education and Sports, Comenius University in Bratislava (Nos. 4/2017 and 1/2020).

The findings obtained will be publicly available in particular journals. Research results will also be presented at scientific conferences and disseminated outside and/or within related healthcare centers and/or universities.

### 2.13. Statistical Analysis

Statistical analysis of the data obtained will be conducted using the SPSS program for Windows, version 24.0 (SPSS, Inc., Chicago, IL, USA). The normality hypothesis will be tested using the Kolmogorov–Smirnov test. A parametric analysis will be conducted if the data are normally distributed. Associations between variables of the perturbation-based balance test and maximal isometric back and hamstring muscle strength in participants with mild to moderate back pain will be assessed using Pearson’s product moment correlation coefficient (small: r = 0.10–<0.30, medium: r = 0.30–<0.50, large: r = ≥ 0.50) [34]. Similarly, the correlation between RFD produced during MVCs of the back and hamstring muscles and postural responses to externally induced perturbations in the control group will be determined. A standard multiple regression analysis will be performed to investigate which of these variables of the muscle strength could be significant predictors of compensatory postural responses to unpredictable stimuli in individuals without back pain. The amount of variance explained will be determined by the coefficient of determination (r^2^). A multivariable logistic regression model will be used to determine associations of back pain (intensity and duration) with the covariates (age, gender, body mass, and eventually psychological factors and/or medical history of participants). The significance level will be set at α = 5%. Data will be presented as the mean (standard deviation).

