## Abstract

Back pain is one of the most costly disorders among the worldwide working population. Within that population, healthcare workers are at a high risk of back pain. Though they often demonstrate awkward postures and impaired balance in comparison with healthy workers, there is no clear relationship between compensatory postural responses to unpredictable stimuli and the strength of related muscle groups, in particular in individuals with mild to moderate back pain. This paper presents a study protocol that aims to evaluate the relationship between peak anterior to peak posterior displacements of the center of pressure (CoP) and corresponding time from peak anterior to peak posterior displacements of the CoP after sudden external perturbations and peak force during a maximum voluntary isometric contraction of the back and hamstring muscles in physiotherapists with non-specific back pain in its early stages. Participants will complete the Oswestry Disability Questionnaire. Those that rate their back pain on the 0–10 Low Back Pain Scale in the ranges 1–3 (mild pain) and 4–6 (moderate pain) will be considered. They will undergo a perturbation-based balance test and a test of the maximal isometric strength of back muscles and hip extensors. We assume that by adding tests of reactive balance and strength of related muscle groups in the functional testing of physiotherapists, we would be able to identify back problems earlier and more efficiently and therefore address them well before chronic back disorders occur.

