### 2.4. Allocation

Participants will be divided into two groups according to the Numeric Rating Scale (mean of three assessments: current LBP, the usual/mean LBP within the last two weeks, and the worst LBP within the last two weeks), which is widely used in medical settings to obtain information about the level of a patient’s pain. The scale ranges from 0 (no pain at all) to 10 (unbearable pain). Participants experiencing mild pain (pain score 1–3), which is easy to manage physically as well as psychologically and does not interfere with most daily activities, and moderate pain (pain score 4–6), which interferes with daily activities and requires changes to manage pain symptoms during the last three months, will be considered. A control group of matched age, gender, and sample size will include those reporting no back pain.

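### Section 2.13 lists no comparison of CoP, peak force or their association between back-pain and control participants, although the study is sized for interactions and matched controls take the same tests

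*Protocol article*

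**What the plan says.** Section 2.13 of the protocol article names four analyses.

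1. In the back-pain group, the association of balance-test variables with "maximal isometric back and hamstring muscle strength in participants with mild to moderate back pain will be assessed using Pearson’s product moment correlation coefficient".
2. In controls, "the correlation between RFD produced during MVCs of the back and hamstring muscles and postural responses to externally induced perturbations in the control group".
3. A standard multiple regression to find which strength variables "could be significant predictors of compensatory postural responses to unpredictable stimuli in individuals without back pain".
4. A multivariable logistic regression of back pain (intensity and duration) on age, gender, body mass and possibly psychological factors or medical history.

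Other sections describe a design with comparable groups. Section 2.4 states that "Participants will be divided into two groups according to the Numeric Rating Scale" (mild and moderate pain) and adds a pain-free control group matched on age, gender and sample size. Section 2.10.2 says "The control group without back pain will undergo the same procedures", with extra fast contractions, and that in controls "the peak RFD in addition to peak force during MVCs of the back and hamstring muscles will be analyzed". Section 2.2 gives 82 participants with back pain and 41 controls. Sections 2.2 and 2.5 both justify the numbers by the ability to detect interactions. The Abstract gives the expected benefit of adding these tests: "we would be able to identify back problems earlier and more efficiently".

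**The concern.** The design has what a group comparison needs: matching, common tests and a sample size justified by interactions. The listed analyses do not make that comparison for either CoP or strength. Nor do they separate mild from moderate pain, although section 2.4 forms those two groups.

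A correlation between peak force and CoP seen only in people with back pain does not show that the tests pick out back problems, because the same correlation may hold in people without pain. The article's Introduction cites earlier work in which lumbar extension strength explained part of the variance of a balance score both in chronic low back pain and in asymptomatic people. The two planned correlations cannot be compared even informally, because one uses peak force and the other RFD. If 2.13 is followed as written, the interactions that justify the sample size are never tested, and the data that could speak to specificity are collected without a planned comparison.

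**Working it through.** **Analyses side by side (section 2.13)**

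| Analysis | Population | Strength measure | Between-group term for CoP or strength |
|---|---|---|---|
| Pearson correlation with CoP | back pain | maximal isometric strength (peak force) | none |
| Correlation with CoP | controls | RFD | none |
| Multiple regression of postural response | no back pain | strength variables, not listed | none |
| Logistic model of back pain | not stated | none | none (no CoP or strength covariate) |

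**The plan's own sample size.** Section 2.5 gives 34 per group at α = 0.05 and 80% power, plus 20%. The inflation reproduces: 34 × 1.20 = 40.8, rounded up to 41, and 2 × 41 = 82. This fits three groups of 41 (mild, moderate, control; 123 in all), although the article does not state how the 82 divide. The 34 itself cannot be checked, because no effect size, standard deviation or test is given.

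**What the planned data could detect if the comparison were added.** Assumptions: two-sided 5% (sidedness is not stated), 80% power, mild and moderate pooled. The multiplier is 1.96 + 0.84 = 2.80.

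Difference in means, in SD units: 2.80 × √(1/n₁ + 1/n₂)
- 82 v 41: 2.80 × √(1/82 + 1/41) = 0.54
- 68 v 34 (2 × 34 and 34, after dropout): 2.80 × √(1/68 + 1/34) = 0.59

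Difference between two independent correlations, Fisher-z scale: 2.80 × √(1/(n₁−3) + 1/(n₂−3))
- 82 v 41: 2.80 × √(1/79 + 1/38) = 0.55
- 68 v 34: 2.80 × √(1/65 + 1/31) = 0.61

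Power for assumed pairs of correlations (back pain v control):

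| Assumed r | 82 v 41 | 68 v 34 |
|---|---|---|
| 0.5 v 0.0 | 79% | 71% |
| 0.5 v 0.1 | 62% | 54% |
| 0.5 v 0.3 | 23% | 19% |
| 0.3 v 0.0 | 35% | 29% |

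The Introduction's cited figures give a rough anchor: about 19.3% to 37.8% of variance explained in chronic low back pain, and 9.5% to 16.9% in asymptomatic people. Treat these as r² and pair low with low and high with high (both assumptions). Then r is √0.193 = 0.44 v √0.095 = 0.31, or √0.378 = 0.61 v √0.169 = 0.41. Power is 12% and 29% at 82 v 41, and 10% and 25% at 68 v 34.

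**Splitting mild from moderate**, assuming 41 per pain group (34 after dropout), for any one pair of groups:
- means: 2.80 × √(2/41) = 0.62, or 2.80 × √(2/34) = 0.68
- correlations: 2.80 × √(2/38) = 0.64, or 2.80 × √(2/31) = 0.71

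A linear model tests a difference in slopes, not in correlations, so the Fisher-z figures are only a rough guide to its interaction term.

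**The case against.** The strongest reply is that the stated objectives are within-group. The Introduction sets two aims: CoP against peak force in physiotherapists with back pain, and rapid force production against postural response in controls. Section 2.13 has an analysis for each. The Abstract's line on earlier identification is worded as an assumption, not as a hypothesis under test. This stands: the listed correlations answer the declared aims and need not be removed.

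Three stronger readings are tempting, and the article does not support them.

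- *The control group adds nothing.* It has its own declared RFD question, repeated in the Discussion.
- *Control peak force goes unanalysed.* Section 2.10.2 says it will be analysed, and the strength variables in the multiple regression may include it. Even so, controls would have a regression and the back-pain group an unadjusted correlation, which is not a like-for-like contrast.
- *Back pain is never contrasted with anything.* The logistic model implies some categorical pain outcome. It relates that outcome only to demographic and history covariates.

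It can also be said that the article condenses a fuller plan and that the reference to interactions suggests a group analysis was intended. That may be so. But the article does not leave the analysis populations open: it names them for the correlations and the multiple regression, and that list conflicts with its own sizing. That RFD is measured only in controls is itself an inference from section 2.10.2, where the fast contractions are described as an addition for that group.

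**Conclusion.** The point holds in this form: section 2.13 lists no between-group analysis of CoP, peak force or their association. This conflicts with the interaction-based sizing in 2.2 and 2.5, the matched and identically tested controls in 2.4 and 2.10.2, and the expected use in the Abstract. The within-group aims are met; specificity to back pain cannot be shown.

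With the data already planned, and pain groups pooled, mean differences of about 0.54 to 0.59 SD are detectable. A difference between correlations must reach about 0.55 to 0.61 on the Fisher-z scale, so the interaction can only be exploratory. These figures assume a two-sided 5% level, 80% power, no covariate adjustment, and either full enrolment or the loss that section 2.5 allows for. They do not give the power of the adjusted model below, and contrasts of mild with moderate pain are less precise. A reader should not infer that the study is adequately sized for an interaction because the article says so: its basis cannot be checked.

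**What to change.** Add to section 2.13, for each of the two primary CoP outcomes (peak-to-peak displacement and the corresponding time), a linear model in all participants. Terms: group, peak force of the back and hamstring muscles, group-by-strength, age, gender and body mass. Report adjusted group differences and group-specific slopes with 95% intervals, and label the interaction exploratory.

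Take peak force from the 5 s trials common to all groups. Drawing on the controls' extra fast contractions as well would give them more attempts from which the best is chosen. State whether group has two levels (pain, control) or three (control, mild, moderate), and how the two stances and the left and right hamstring values enter. Keep the existing within-group correlations, and keep RFD as a controls-only analysis. Align the sample-size wording in 2.2 and 2.5 with the model.

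The cost is analysis wording only, with no further participants or tests. The downside is a larger model with an imprecise interaction. With two strength measures and three groups it has 12 coefficients (1 intercept + 2 strength + 2 group + 4 interaction + 3 covariates); with pain pooled it has 9 (1 + 2 + 1 + 2 + 3).

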## 3. Discussion

Therapists in health care, including physiotherapists, physical therapists, and athletic therapists, are at high risk of developing LBP [1,3,35,36,37]. The occurrence of back problems will likely rise as patients become heavier with increasing obesity. Therefore, more efforts should be directed toward their prediction by regular assessment of physical factors associated with back pain in its early stages. Among them are those associated with awkward spinal postures, impaired static and dynamic balance, and reduced core and lower limb strength. However, conflicting evidence exists on associations among these performance determinants and the occurrence of back problems.

For instance, a significant relationship was demonstrated between the percentage of time spent in awkward postures in the sagittal plane (trunk flexion ≥45°) and in the frontal plane (lateral bend ≥20°) and LBP in hospital nurses [38]. However, a systematic review by Roffey et al. [39] revealed that there is no association between awkward postures and LBP and that there is no temporal relationship. Weak associations and no evidence for other aspects of causality in certain specific subcategories were demonstrated in few studies [39]. Therefore, it is unlikely that awkward occupational postures are independently causative of LBP in the working population [39].

Further, individuals with LBP often exhibit altered responses to sudden perturbations. In particular, delayed trunk muscle responses [40,41,42], decreased amplitudes of muscle activation [40,43], and increased co-contraction [40] are associated with the occurrence of LBP. However, most studies investigating postural responses to perturbations applied to the body’s trunk have been limited to electromyographic (EMG) recordings while less attention has been paid to the assessment of muscle strength and power.

The trunk and hip muscle strength contributes to lumbar spine stability, particularly during functional tasks. Additionally, a low level of the trunk muscle co-contraction is important for the body’s core stability [44]. Such a level of stiffness provides necessary stability against minor perturbations. In particular, direction-specific muscle reflex responses play an essential role in the stability of the body’s core when encountering unexpected postural perturbations [44].

The evidence has demonstrated that shortening, weakness, and/or muscle stiffness of the pelvic and lumbar regions contribute to LBP. There is an association between decreased stability and an increased risk of low back or knee injury [44]. These individuals demonstrate impaired postural stability, abnormal recruitment patterns of the trunk muscles, and delayed muscle reflex responses to unexpected trunk unloading [44]. Additionally, lower strength of knee extensors and hip abductor/extensors has been reported in LBP patients than healthy controls [45,46,47,48,49]. Provided that the muscles of lower limbs, particularly the hip muscles, play an important role in the stability of the lumbar spine [50], it is likely that lumbar instability and inefficient lumbopelvic motor control, together with weakness in hip muscles, may contribute to LBP development. However, a relationship between hip strength and back pain has not been found [51,52].

Thus far, the association of hip weakness with the presence of non-specific LBP has not been sufficiently investigated. Although several studies have demonstrated the efficiency of trunk and lower limb strengthening exercises for improvement of core stability [53,54,55], less attention has been paid to core stability in relation to the strength of particular muscle groups. This is due to a paucity of easy to administer tests using portable and user-friendly diagnostic systems suited for testing in field conditions.

Our study will address this gap in the available research. It will provide insight into the association between the ability of subjects to maintain postural stability after an unexpected perturbation and maximal isometric strength of the back and hamstring muscles. Our attention will be paid to healthcare workers, namely physiotherapists with mild to moderate non-specific back pain in whom it is hard to reveal slight impairments of the ability to regulate CoM motion using less sophisticated non-laboratory techniques. Identifying the relationship between these factors will help us to design a test battery tailored specifically for this high-risk population using tests that can be performed in field conditions. The limitation will be the sample consisting of mainly female participants due to larger number of women working in the healthcare sector. However, the LBP prevalence rate in this population is high, with the majority of cases occurring after starting work [3,56].

In addressing LBP prevention, the ability to produce maximum force in a short period of time during MVCs of the back and hamstring muscles will be assessed in the control group without back pain. This method could provide feedback about whether those with higher peak RFD during MVC of relevant muscle groups are capable of responding effectively to unexpected postural perturbations. It can be implemented in healthy subjects who may benefit from such testing by predicting their LBP risk. Revealing impaired postural and/or core stability and reduced strength of relevant muscle groups could support self-help strategies in the prevention of back problems by the application of hip–trunk stabilization and strengthening exercises in their daily activities. This may contribute to a reduction in chronic back problems and consequently lowering healthcare system costs.

## Figures and Tables

**Figure 1 ijerph-18-05578-f001:**
[figure not shown]
Flowchart of the study design.
